## Abstract

Background: Nerve entrapment has been hypothesized to contribute to the multicausal etiology of axonopathy in sensorimotor diabetic neuropathy. Targeted surgical decompression reduces external strain on the affected nerve and, therefore, may alleviate symptoms, including pain and sensory dysfunction. However, its therapeutic value in this cohort remains unclear. Aim: Quantifying the treatment effect of targeted lower extremity nerve decompression in patients with preexisting painful sensorimotor diabetic neuropathy and nerve entrapment on pain intensity, sensory function, motor function, and neural signal conduction. Study design: This prospective, controlled trial studies 40 patients suffering from bilateral therapy-refractory, painful (*n* = 20, visual analogue scale, VAS ≥ 5) or painless (*n* = 20, VAS = 0) sensorimotor diabetic neuropathy with clinical and/or radiologic signs of focal lower extremity nerve compression who underwent unilateral surgical nerve decompression of the common peroneal and the tibial nerve. Tissue biopsies will be analyzed to explore perineural tissue remodeling in correlation with intraoperatively measured nerve compression pressure. Effect size on symptoms including pain intensity, light touch threshold, static and moving two-point discrimination, target muscle force, and nerve conduction velocity will be quantified 3, 6, and 12 months postoperatively, and compared (1) to the preoperative values and (2) to the contralateral lower extremity that continues non-operative management. Clinical significance: Targeted surgical release may alleviate mechanical strain on entrapped lower extremity nerves and thereby potentially improve pain and sensory dysfunction in a subset of patients suffering from diabetic neuropathy. This trial aims to shed light on these patients that potentially benefit from screening for lower extremity nerve entrapment, as typical symptoms of entrapment might be erroneously attributed to neuropathy only, thereby preventing adequate treatment.

## 1. Introduction

Nowadays, 1 in 11 adults, or about 463 million people worldwide, are estimated to suffer from diabetes, a number that has more than tripled over the past 2 decades [1]. Consequently, approximately one-tenth of global health expenditures, equaling USD 760 billion, are spent on diabetes [1]. Up to 50% of those diabetic patients worldwide eventually develop peripheral diabetic neuropathy [2], rendering diabetes the most common cause of neuropathy to date [3].

The progressive neurodegeneration in diabetic neuropathy occurs in a length-dependent fashion and primarily affects sensory and autonomic axons of the peripheral nervous system [4]. This causes sensory dysfunction and, in one-third of the affected patients, severe and persistent pain [5,6,7]. Particularly, distal axon terminals including intraepidermal nerve fibers are affected first, proceeding to proximal axonal degeneration [5]. Although the pathomechanism of this characteristic pattern of neurodegeneration is subject to an ongoing debate, glucotoxicity, inflammation, progressive intraneural microangiopathy, and impaired neuronal and Schwann cell metabolism are likely involved [8,9,10,11,12].

Beyond these mechanisms, previous work indicated that progressive intra- and extraneural fibrotic tissue remodeling [13,14,15,16,17,18], similar to diabetes-associated fibrosis observed in multiple parenchymal organ systems, affect the mechanical properties of the nerve and surrounding tissues [19,20,21,22]. Accordingly, neurosonographic studies observed a significant increase in circumference and stiffening of peripheral nerves in patients with diabetic neuropathy, associated with an increase in connective tissue in the endoneurium [13,14,15,16,17,18]. This supports the idea that axonal degeneration secondary to diabetes may be promoted by mechanical nerve entrapment in some patients. Given the hyper-excitability and altered stimulus–response function in sensory neurons of diabetic individuals [23,24], external pressure on the neuropathic nerve may promote sensory dysfunction and pain in these patients.

In advanced diabetes, intraneural capillary dysfunction and consequently impaired oxygen extraction, combined with phenotypic alterations in mitochondrial biology in diabetic neurons, result in reduced adaptability to fluctuating energy demand and, thus, may cause exhaustion of the ATP supply in distal axonal components [9]. Chronic compression further reduces nerve perfusion and thereby its nutrient supply, promoting a hypoxic proinflammatory environment [10,11,25,26], thus, likely contributing to Schwann cell impairment and axonal injury at the compression site.

Therapeutic options are limited for this debilitating disease. In the United States, all clinical trials that aimed to prevent disease progression of diabetic neuropathy have failed so far [27]. Modifying symptom severity has been equally challenging, as even state-of-the-art pain medication may achieve an average individual pain reduction of only 30–50% in these patients [28,29]. The consequent enormous socioeconomic burden of this disease, at a personal and societal level, mandates interdisciplinary management of these patients, taking advantage of all available therapeutic options. This trial aims to investigate the surgical release of entrapped lower extremity nerves in selected patients with diabetic neuropathy as an adjunct therapeutic option to address the compressive component of this multifactorial disease and, therefore, may alleviate pain and improve sensory function.

## 2. Study Objectives

The primary objective of this trial is quantifying the treatment effect size of unilateral surgical release of the tibial nerve in the tarsal tunnel and/or the common peroneal nerve below the muscle fasciae in the proximal lower leg [30] on pain intensity, analgesics consumption, and sensory dysfunction in the skin area supplied by the decompressed nerves.

Secondary objectives are quantifying the treatment effect on target muscle force and fatigability, as well as the incidence of diabetic ulcers in the skin area supplied by the decompressed nerve. Furthermore, tissue biopsies from the perineural fat and overlying compressive fascia are analyzed to explore perineural tissue remodeling in correlation with intraoperatively measured tissue pressures in nerve constriction sites.

Trial registration: German Clinical Trials Register (DRKS); DRKS-ID: DRKS00021151.

## 3. Materials and Methods

### 3.1. Participants, Eligibility Criteria

A total of 40 type 1 and type 2 diabetic patients (age 18–90 years) suffering from diabetic sensorimotor neuropathy and showing clinical signs of compression of the tibial nerve in the tarsal tunnel and/or the common peroneal nerve below the muscle fasciae in the proximal lower leg on both lower extremities are included in this trial. Of those, *n* = 20 participants suffer from therapy-refractory pain with intensities of 5 and greater on the visual analogue scale (VAS), and another *n* = 20 participants suffer from therapy-refractory hypoesthesia, predominantly localized in the skin areas supplied by the potentially entrapped peripheral nerves.

Detailed eligibility criteria for participating in this trial are as follows:Age 18–90 years;Type 2 or type 1 diabetes mellitus diagnosed according to the guidelines of the German Diabetes Association [31].

And
Diabetic sensorimotor polyneuropathy of both lower extremities [32]:
-Neuropathy Deficit Score > 5 points;-Neuropathy Deficit Score 3–5 points + Neuropathy Symptom Score > 4 points.

And
Clinical evidence of bilateral local nerve compression of the tibial nerve in the tarsal tunnel and/or the common peroneal nerve under the muscle fascia of the peroneus longus muscle:
-Predominant focal (pain) symptoms in the innervation area of the nerve distal to the compression site;-Hoffman–Tinel’s sign over the compression site;-Characteristic electrodiagnostic findings of compression e.g., local conduction block;-Characteristic findings of compression in the MR-neurography, e.g., local T2 weighted hyperintensity of the nerve within the compression site.

And
Bilateral, therapy-refractory pain in the area supplied by the potentially entrapped nerve under conventional, guideline-compliant analgesic therapy (VAS >5);Bilateral hypesthesia in the area supplied by the potentially entrapped nerve defined as a tactile perception threshold greater than 6 g but less than 60 g.Exclusion criteria are as follows:HbA1c in the blood plasma > 8.5% (i.e., poor disease control);Reduced ability to give consent and/or legal capacity (e.g., due to mental illness);Contraindications to lower extremity surgery;Contraindications for electrodiagnostics, such as implanted cardiac pacemaker/defibrillator;Diseases that potentially confound the outcomes of interest, in particular:
-Other diseases of the peripheral or central nervous system not mentioned under “Inclusion criteria”;-Moderate or severe peripheral arterial disease (ankle–brachial index <0.75, or missing foot pulses from the dorsal pedis artery or posterior tibial artery on at least one lower extremity);-Dermatological conditions of the lower extremities.

### 3.2. Intervention

Patients with diabetic sensorimotor neuropathy of both lower extremities and signs of bilateral tibial nerve and/or peroneal nerve entrapment undergo unilateral decompression of the entrapped nerve(s) (Figure 1A–H) by an experienced senior microsurgeon ([name]). Intraoperatively, prior to surgical release, the nerve compression pressure is measured by inserting a CE-certified flexible pressure probe (Mikro-Cath, Millar, Houston, TX, USA) into the anatomical constriction site (Figure 1B,F,G).

A tourniquet is used to improve intraoperative visibility. Decompression of the tibial nerve in the tarsal tunnel is conducted through an 8–10 cm long skin incision on the inner malleolus (Figure 1A). The tarsal ligament is split and partially resected to avoid recurrence. The medial and lateral plantar nerves are then released as they pass under the deep fascia of the abductor hallucis muscle. The tibial nerve is carefully mobilized from the surrounding tissue and the decompression is verified by subsequent elevation of the nerve (Figure 1C) [30,33].

The common peroneal nerve is decompressed through a 5–7 cm long skin incision around the fibular head and neck (Figure 1D,E). The nerve is traced distally, and the compressing fasciae are split, namely the fascia of the peroneus longus muscle, the posterior and anterior crural intermuscular septum, the intermuscular septum between the extensor digitorum longus and tibialis anterior, and the fascia of the soleus muscle, including any accessory bands of connective tissue along the nerve (Figure 1H). Decompression is verified by subsequent elevation of the nerve.

Intraoperatively, tissue biopsies are harvested from (1) the tarsal ligament, (2) the fascia of the peroneus longus muscle, and (3) the perineurial tissue of the decompressed nerves(s) for subsequent analysis. A meticulous bipolar hemostasis is carried out with subsequent multi-layered skin closure using surgical sutures.

The surgery is performed as an inpatient procedure, using postoperative compressive dressings, daily wound care, and a slightly elevated position of the operated limb for 48 h post-surgery to reduce postoperative swelling and risk of hematoma.

### 3.3. Outcomes

#### 3.3.1. Pain Intensity

Participants are asked to quantify pain intensity using the numeric rating scale (NRS) in the skin areas supplied by the entrapped peripheral nerves in each lower extremity, preoperatively as well as 3, 6, and 12 months postoperatively.

#### 3.3.2. Sensory Function

Participants undergo sensory testing in the skin areas supplied by the tibial and peroneal nerves (Figure 2) in both lower extremities preoperatively, as well as 3 and 12 months postoperatively.

##### Tactile Sensory Threshold

The tactile sensory threshold describes the lowest detectable light touch stimulus. For this trial, it is assessed according to the protocol of the German Research Association for Neuropathic Pain (DFNS) [34] using a set of standardized CE-certified von Frey hairs (8, 16, 32, 64, 128, 256, and 512 mN). The geometric mean value of the tactile detection threshold is determined in five series using a modified limit value method (“method of limits”) based on decreasing stimulus intensities.

##### Two-Point Discrimination

Two-point discrimination describes the ability to recognize two stimuli as two individual stimuli (and not one stimulus) when they are simultaneously applied in close proximity. Static and dynamic two-point discrimination are assessed in a participant-blinded fashion using a two-point esthesiometer (NCD Medical/Prestige, Los Angeles, CA, USA) according to the protocol of Dellon and Mackinnon [35]. The esthesiometer is placed on the skin with its own weight (10 g), so that the skin is minimally deformed to a standardized extent. The dynamic two-point discrimination assessment follows the same protocol; however, the stimuli are slowly and uniformly moved over the skin in the examination area over a 1.5 cm distance, without applying additional pressure. Two-point discrimination is defined as the minimum distance between two stimuli in millimeter that is correctly recognized as two stimuli in two out of three applications.

##### Quantitative Sensory Testing (QST)

Additionally, participants undergo standardized quantitative sensory testing (QST) on both lower extremities according to the protocol of the German Research Network on Neuropathic Pain (DFNS) [36] preoperatively, and at least one year postoperatively. Complete QST determines neuropathic deficits in 13 different categories, including cold detection threshold, warm detection threshold, thermal sensory limen, cold pain threshold, heat pain threshold, pressure pain threshold, mechanical pain threshold, mechanical pain sensitivity, wind-up ratio, mechanical detection threshold, vibration detection threshold, dynamic mechanical allodynia, and paradoxical heat sensation.

#### 3.3.3. Motor Function

Maximum isometric muscle strength and fatigability of movements that involve the target muscles of the entrapped tibial and peroneal nerves are assessed in both lower extremities preoperatively, as well as 3 and 12 months postoperatively.

To assess for a potential therapeutic effect of surgical decompression of the tibial nerve in the tarsal tunnel, the maximum isometric muscle strength of great toe flexion is measured using a handheld dynamometer (MicroFET 2, Hoggan Scientific, Salt Lake City, UT, USA). The peroneal nerve’s target muscles are assessed using the maximum isometric muscle strength of great toe extension.

The dynamometer is placed perpendicular to the direction of the force vector and the application points of the dynamometer are standardized using anatomical landmarks. The patient is then instructed to perform the movement to be tested and to maximally press against the force absorbing plate of the dynamometer for a period of five seconds while avoiding explosive movements. The examiner stabilizes the limb proximal to the limb segment to be tested. Three repeat tests are then carried out with approximately 30 s rest in-between. The maximum isometric force mean and the peak values are documented [37].

Muscle fatigability and coordination are assessed using the one-legged toe stand test. Participants perform a repeated concentric–eccentric muscle contraction of the plantar flexors in a one-legged stand [38,39]. The cadence of the toe stands is acoustically specified with a metronome at 60 per minute. Subjects are instructed to maximally raise the heel on each repetition while keeping the knee extended and the trunk upright. The test ends when the subjects can no longer (completely) lift the standing heel or when they can no longer maintain the set pace, knee angle, or trunk position. The number of correct heel raises is counted for each leg and recorded.

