### 3.8. Data Management and Statistics

The collected data will be pseudonymized using case report forms with a unique participant number. Before publication and during statistical analysis the data will be completely anonymized. All collected data are analyzed using descriptive statistics (absolute and relative frequencies or mean, standard deviation, median, interquartile range (IQR), and, if necessary, confidence intervals), and graphic methods to characterize distributions. Because intervention and control group measurements are obtained from one subject and are collected in serial measurements over time, the data are analyzed as matched samples using signed-rank tests to address the following hypotheses.

The targeted surgical release of a mechanically compressed nerve in diabetic, sensorimotor polyneuropathy results in the following:A reduced pain intensity in the innervation area of the nerve distal to the decompression site 3, 6, and 12 months postoperatively, compared to the preoperative pain intensity and compared to an intraindividual non-decompressed control (contralateral lower extremity).A reduced analgesics consumption 3, 6, and 12 months postoperatively, compared to the preoperative baseline.Improved sensation (two-point discrimination, tactile detection threshold) in the innervation area of the nerve distal to the decompression site 3 and 12 months postoperatively compared to the preoperative situation and compared to an intra-individual, non-decompressed control (contralateral lower extremity).Increased isometric muscle strength in target muscles supplied by muscle branches arising from the decompressed nerve distal to the decompression site, 3 and 12 months postoperatively, compared to the preoperative situation and compared to an intra-individual, non-decompressed control (contralateral lower extremity)An increase in nerve conduction velocity across the decompression site 3 and 12 months postoperatively compared to the preoperative situation and compared to an intra-subject non-decompressed control (contralateral lower limb).A lower prevalence of neuropathic ulcerations in the innervated skin area of the nerve distal to the decompression site compared to an intra-individual, non-decompressed control (contralateral lower extremity) in the 12-month postoperative follow-up period.

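### The only fatigability test, the heel raise, mainly loads calf muscles supplied above the tarsal tunnel release, so it does not measure target-muscle fatigability; great-toe flexion measures tibial target-muscle strength only in part

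*Protocol article*

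**What the plan says.** Section 2 sets the objective: "Secondary objectives are quantifying the treatment effect on target muscle force and fatigability".

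Section 3.8 states the motor hypothesis and, in doing so, says which muscles count as targets: "Increased isometric muscle strength in target muscles supplied by muscle branches arising from the decompressed nerve distal to the decompression site".

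Section 3.2 fixes the level of the tibial operation: "Decompression of the tibial nerve in the tarsal tunnel is conducted through an 8–10 cm long skin incision on the inner malleolus". It continues downwards into the foot: "The medial and lateral plantar nerves are then released as they pass under the deep fascia of the abductor hallucis muscle". The peroneal nerve is released separately, around the fibular head and neck.

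Section 3.3.3 names the tests:
- Fatigability: "Muscle fatigability and coordination are assessed using the one-legged toe stand test". The movement is described as follows: "Participants perform a repeated concentric–eccentric muscle contraction of the plantar flexors in a one-legged stand".
- Tibial strength: "the maximum isometric muscle strength of great toe flexion is measured using a handheld dynamometer".
- Peroneal strength: "target muscles are assessed using the maximum isometric muscle strength of great toe extension".

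Sections 2 and 3.1 allow compression or release of the tibial nerve, the common peroneal nerve, or both.

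**The concern.** A motor test can show whether a released nerve has recovered only if it loads muscles that the nerve supplies beyond the point of release. The heel raise is the sole fatigability test, and its main movers lie in the calf, above the ankle-level release. If the plan is followed as written, a general-function result will be reported as the effect of decompression on target-muscle fatigability.

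Both possible results would then be misread. A null would be taken as no effect on fatigability of the target muscles, although these were hardly tested. A gain would be taken as motor recovery of the nerve, although less pain on loading, better balance or more effort could produce it. Effort is a real possibility: under Section 3.7 the patient's preference decides which leg is operated on, and the blinding described is that of the examiner.

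The Discussion criticises earlier studies for judging pain over the whole limb and not over the territory of the decompressed nerves, so that mechanism could not be established. The heel raise brings a similar weakness into the motor outcomes.

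**Working it through.** No stated figure is in dispute, so the main check sets the sections side by side. Branch levels are general anatomy. The release sites, the tests and the distal criterion come from the protocol.

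**Step 1. Match each test to the release.**

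| Test (3.3.3) | Main muscles loaded | Where the nerve supply leaves | Meets the distal criterion of 3.8? |
|---|---|---|---|
| Heel raise | Gastrocnemius, soleus | Tibial nerve, well above the ankle | No for the main movers |
| Great-toe flexion | Long flexor; short flexor and abductor hallucis | Long: calf, above the tunnel. Short flexor and abductor: medial plantar nerve, released under 3.2 | In part |
| Great-toe extension | Toe extensors | Peroneal nerve, beyond the fibular neck | Yes |

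The peroneal operation does not rescue the heel raise. It splits the soleus fascia, but to free the common peroneal nerve, which does not supply soleus. The peroneal muscles assist plantar flexion without being the main movers.

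**Step 2. What dilution could do to great-toe flexion (illustration only).**

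Section 3.5 gives 20 patients per stratum, power above 0.8, a 5% level and 20% drop-out, but neither effect size nor standard deviation. The sample size therefore cannot be reproduced from the article. Working backwards:
- Evaluable pairs per stratum: 20 × (1 − 0.20) = 16.
- Effective number for a signed-rank test, assuming relative efficiency 0.955: 16 × 0.955 = 15.28.
- Smallest paired standardized effect with 80% power, two-sided 5%: 0.77 (noncentral t, noncentrality d × √15.28 = 0.77 × 3.909 ≈ 3.01).

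Now let the muscles supplied below the release have a true standardized effect of 0.77 and contribute a share s of the measured effect, with the standard deviation of the score unchanged. The visible effect is s × 0.77.

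| s | Visible effect | Power with 16 pairs |
|---|---|---|
| 1 | 0.77 | 80% |
| 0.75 | 0.58 | about 56% |
| 0.5 | 0.385 | about 29% |
| 0.25 | 0.19 | about 10% |
| 0 | 0 | no more than the 5% level |

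The protocol does not give s, and nothing in it bounds s. The table shows only how quickly a null loses meaning when the measured force is a mixture.

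**Step 3. The choice of nerve.** Where only one nerve is released, the toe test for the other nerve has no released supply in that patient. Pooling all patients would add a second dilution. The Abstract reads as if both nerves are released in everyone; if so, this step changes nothing.

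**The case against.** Much can be said for the plan.

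- **The distal criterion sits in the strength hypothesis.** Fatigability is not among the hypotheses of Section 3.8, and Section 3.3.3 says only that the target muscles take part in the movements tested. This is true and limits the charge: no formal fatigability hypothesis fails. But Section 2 names target-muscle fatigability as an objective, and Section 3.8 is the only place that says what a target muscle is. The mismatch remains.
- **Other neural routes to the heel-raise count exist.** The peroneal muscles help plantar flexion, intrinsic foot muscles bear load on a raised heel, and sensation of the sole may aid balance in a test that Section 3.3.3 also uses for coordination. This stands. A reader might infer that the neural effect must be exactly zero in all 40 patients; the documents support only a small expected effect.
- **Great-toe flexion can respond.** This stands too. A reader might conclude that the tibial motor question cannot be answered at all. It can, because Section 3.2 releases the plantar nerves and the medial one supplies the short flexor. The strength hypothesis is weakened, not lost.
- **The device is already standardized.** Section 3.3.3 fixes application points by anatomical landmarks. The exact landmark is detail for the full protocol, and no fault is found there.
- **The trial generates hypotheses.** The Discussion leaves confirmation to later studies. This lowers the severity, but a mislabelled outcome can still produce a wrong hypothesis.

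**Conclusion.** Wrong as written, of moderate to minor severity. The heel raise does not measure target-muscle fatigability in the sense the protocol itself gives to target muscles, and no other fatigability test is named. Any neural effect of decompression on it is expected to be small; no figure can be put on that from the documents. Great-toe flexion is a partial target measure, diluted to an unknown degree. Great-toe extension is well placed.

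The conclusion rests on general anatomy for the branch levels and on the protocol for everything else. The power figures rest on assumed values (16 pairs, effect 0.77, efficiency 0.955, unchanged standard deviation) and are not needed for it.

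It might seem a natural next step to keep the heel raise as a negative control for effort and expectation. The protocol does not support that use. Pain relief is a primary intended effect and can itself raise the count, so a true benefit could be mistaken for bias.

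**What to change.** Reconcile Sections 2, 3.3.3 and 3.8:

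1. Report heel raises as a general lower-limb function outcome, neither as target-muscle fatigability nor as a negative control.
2. Drop the target-muscle fatigability objective in Section 2, or restrict it to what the test can show.
3. Describe great-toe flexion as a partial target measure, and state that a null does not exclude recovery of the muscles supplied by the plantar nerves.
4. Analyse great-toe flexion only in patients with a tibial release and great-toe extension only in those with a peroneal release, comparing the operated with the contralateral leg.

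This changes wording and the assignment of patients to analyses, with no new visit, device or test. There are two small costs. The trial no longer claims an efficacy outcome for target-muscle fatigability, and each toe test may rest on fewer pairs if some patients have only one nerve released.
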